#### Waiting list control

Participants will be placed on a waiting list for 14 months (matching the participation duration of participants in the other conditions; 8-week intervention period plus 1 year follow-up), after which they will be offered 8 weeks of Featback with support from an expert patient. Participants in this condition will be asked to complete the same assessements as participants in the other conditions (i.e., T0-T5). Note that participants in all conditions are allowed to seek and receive treatment and take medication.

#### Intervention check

To assess the difference between support by expert patients and psychologists, a formal integrity check will be conducted. After data collection, 15 randomly selected chat and 15 e-mail sessions of expert patients will be compared to 15 randomly selected chat and 15 e-mail sessions of psychologists respectively (taken from the previous RCT of this research group; 20). Subsequently, three independent master level psychology students, blind to the source of the e-mail or chat session, will rate the 60 sessions with the integrity list. Expert patients and psychologists collaborated to create the integrity checklist, which involves (1) the structure of the session, (2) the content/interventions used during the session, and (3) the way in which these interventions were conveyed (see Additional file 2). We expect that the structure of an e-mail or chat is similar between expert patients and psychologists, since the same structuring methodology is used. However, psychologists are expected to use a broader pallet of interventions (i.e., more distinct interventions) during the e-mail and chat support. Lastly, the most noticeable difference is expected in the way in which interventions are conveyed. More specifically, it is hypothesized that expert patients will explicitly mention their own experiences during every e-mail or chat session to try to change attitudes or behaviors of participants, whereas psychologists will never do this. Additionally, expert patients are expected to use fewer medical terms or abbreviations in their e-mail or chat sessions than psychologists.

### Measures

Table 2 presents an overview of the assessment instruments used for each measurement time. Estimated times (minutes) to complete each questionnaire are presented in parentheses. Details of the instruments are described in the following sections.

**Table 2 Tab2:**
[figure not shown]
Overview of assessment occasions and their content

*Note*: The Inclusion of Other in the Self scale (IOS scale; 0.5 min to complete) will be sent at week 3 of the intervention for all participants in a condition with expert-patient support. Attrition follow-up questions will be sent only to participants who do not respond to the assessments

*FU* follow-up, *WCS* Weight Concerns Scale, *SEED* Short Evaluation of Eating Disorders, *PHQ-4* Patient Health Questionnaire, *EDE-Q* Eating Disorder Examination Questionnaire, *GSES* General Self-Efficacy Scale, *SSL* Social Support List, *RSES* Rosenberg Self-Esteem Scale, *EQ-5D-5 L* EuroQol five dimensions, five levels generic health index, *ICECAP-A* ICEpop CAPability measure for Adults, *TiC-P MIDI* Trimbos/iMTA questionnaire for Costs associated with Psychiatric Illness Midi version, *PCQ* Productivity Costs Questionnaire

#### Screening measures

##### Weight Concerns Scale

The Weight Concerns Scale (WCS [54]) is a five-item questionnaire used to evaluate the eligibility of participants. The five items are derived from a principal component analysis of a list of questions used to measure ED symptoms [54] and assess the extent to which participants struggle with their weight, eating pattern, shape, and perceived corpulence. Test-retest reliability and predictive validity have been investigated and demonstrated for the WCS [57]. Furthermore, the WCS has been found to be able to predict students at risk for developing an ED [58].

##### Short Evaluation of Eating Disorders

The Short Evaluation of Eating Disorders (SEED [55]) contains six self-report questions designed to quickly assess the key ED symptoms. Participants are asked to evaluate their own body on several dimensions (e.g., thinness, attractiveness, and muscularity) and to report the frequency of several ED-related behaviors, such as self-induced vomiting, use of laxatives, and binge eating, over the last 4 weeks. Items are presented on a 5-point Likert scale. Summing the items of the two separate diagnoses leads to a severity index (range 0–3), with higher scores indicating higher severity. The SEED has been found to have good construct and criterion validity and was demonstrated to be sensitive to symptom change [55].

#### Primary outcome measures

The primary outcome measures involve the Eating Disorder Examination Questionnaire (EDE-Q [59]), which will be used to assess ED symptomatology. The EDE-Q has 28 items and assesses both the frequency of core ED behaviors (6 items) and ED-related attitudes (22 items) over the past 28 days. Items assessing the ED-related attitudes are presented on a 7-point Likert scale (range 0 ”not at all” to 6 ”every day/markedly”) and include questions regarding weight, shape, and eating concerns and restraint. A global ED psychopathology score will be calculated by summing and averaging the 22 items. Higher scores indicate higher ED psychopathology. Internal consistency, test-retest reliability, and discriminative validity of the EDE-Q have been found to be acceptable to high [60].

#### Secondary outcome measures

##### General Self-Efficacy Scale

The General Self-Efficacy Scale (GSES [61]) is a 10-item psychometric scale designed to measure a general sense of perceived self-efficacy with the aim to predict coping with daily hassles and adaptation after experiencing various stressful life events. The questionnaire has been used in many studies with numerous participants [62]. Responses are recorded on a 4-point scale. The individual items are summed to produce the final composite score with a range of 10 to 40. In samples from 25 nations (including the Netherlands), Cronbach’s *α* ranged from 0.75 to 0.91, with most values over 0.80. Psychometric properties of the GSES are adequate [63]. The scale is one dimensional and designed for the general adult population, including adolescents.

##### Social Support List

Perceived social support is measured with the short version of the Social Support List Interaction (SSL-12-I [64]). This self-report questionnaire measures the extent to which a participant experiences social support. The SSL-12-I contains 12 items in three scales, namely (1) everyday social support, (2) support in problem situations, and (3) esteem support (i.e., support resulting in self-esteem). Items (starting with ”Does it ever happen that people…” and ending with statements like ”…comfort you?” or ”…give you good advice?”) are presented on a 4-point scale ranging from ”hardly or never” to ”very often”. Scores range from 12 to 48, and higher scores are indicative of more experienced social support. Psychometric properties are demonstrated to be good [64, 65].

##### Patient Health Questionnaire

The Patient Health Questionnaire (PHQ-4 [66]) measures symptoms of depression and anxiety. It consists of two primary anxiety items and two primary depression items. The anxiety and depression subscales have been found to reflect two separate dimensions [66]. The four items are presented on a 4-point Likert scale ranging from 0 ”not at all” to 3 ”nearly every day”. By summing all items, a composite score (range 0–12) can be calculated. Higher scores indicate higher pathology. The PHQ-4 has been demonstrated to possess factorial and construct validity [66].

##### Motivation to change

Three items will be used to assess participants’ motivation to change [67, 68]. The first item assesses the perceived importance to change of participants (*On a scale of 1 to 10, how important is it for you to change?*)*.* The second item assesses the ability or confidence to change (*On a scale of 1 to 10, how confident are you that you could make a change if you wanted to?*)*.* The third item assesses one’s readiness to change (*On a scale of 1 to 10, how ready, or how prepared are you to change? Are you not prepared to change, already changing, or somewhere in the middle?*)*.*

##### User satisfaction

To assess the user satisfaction of Featback, a questionnaire was developed. Among other questions, participants are asked how they rate the quality of support they have received from Featback, whether Featback helped them to more effectively cope with their eating-related problems, and the extent to which they were satisfied with Featback in general. Additionally, participants are requested to rate the various components of Featback and address positive points as well as points for improvement (e.g., they are asked what they liked or disliked most and how the intervention can be developed further).

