Naturally, there are limitations to low-threshold Internet interventions aimed at prevention and early intervention of EDs in the extent to which they can respond to the personal situation of users, especially when compared with interventions in which intensive and direct contact with a professional is possible, such as blended care. Nevertheless, it is important for low-threshold Internet-based interventions not to employ a ”one-size-fits-all” approach. Indeed, not everyone profits from or prefers the same content of treatment, and the Internet is a highly suitable medium to convey interventions in a flexible and interactive way. The Internet-based program ”Featback” combines prevention and (early) intervention for individuals with ED symptoms. The program aims to make users aware of their eating-related and underlying problems. Users are encouraged to share their problems with their environment and, for more severe problems, to seek professional help. The program can be used anonymously, reducing the barrier to subscribe. It contains psychoeducation, a fully automated symptom monitoring and feedback system, and weekly chat or e-mail contact with a coach. A more detailed account of Featback is presented in the “Interventions” section of this article. Featback is based on ES[S]PRIT [14], a program originally developed in Germany. Research on ES[S]PRIT suggested the intervention is both feasible [14] and acceptable [15] and improves self-efficacy in young individuals with ED-related problems [16] and enhances help-seeking behaviors [17, 18].

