## Methods

### Design

Since the present study is a continuation of previous work of this research group, the methodology described here will be similar and in some parts identical to the previous design [19]. The current study describes an RCT with a two-by-two factorial design with repeated measures to create four different conditions: (1) Featback, comprising psychoeducation and a fully automated self-monitoring and feedback system, (2) Featback with weekly individualized support by an expert patient through e-mail or chat, (3) weekly individualized support by an expert patient through e-mail or chat, and (4) a waiting list. A description of the content of the interventions for each condition is presented below. After screening, all eligible participants are asked to give informed consent and fill in online baseline measures (T0). Subsequently, they will be randomized to one of the four conditions. An independent researcher will conduct randomized allocation by using the SPSS function to produce random numbers. Hence, the main researcher will be blind to the randomization process. Randomization will take place in blocks of 40 participants. The current design does not allow expert patients to be blinded to the study goal, since they are required to help participants with their ED or ED-related problems to the best of their abilities within the intervention protocol. Naturally, expert patients know that the individuals they have contact with via e-mail or chat are randomized to one of the expert-patient support conditions. Similarly, participants are not blinded concerning the condition allocation.

After 8 weeks (intervention period or waiting period), participants are invited to complete the post-intervention assessment (T1). Finally, a link to the online follow-up questionnaires will be sent to them 3 (T2), 6 (T3), 9 (T4), and 12 (T5) months after T1 (see Fig. 1). Ethical approval has been obtained by an independent medical ethics committee (CME LUMC Leiden, file number NL64553.058.18). The Standard Protocol Items: Recommendations for Interventional Trials (SPIRIT) checklist is provided as Additional file 1.

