##### Help-seeking attitudes and behavior questionnaire

A custom-made questionnaire was developed to assess help-seeking attitudes and behaviors. Participants are presented with three 7-point Likert scale questions (ranging from 0 ”not at all applicable” to 6 ”fully applicable”) concerning the extent to which they believe professional help is useful, they need professional help themselves, and they know where to find help. Furthermore, intention to seek professional help and actual help-seeking behavior are assessed, and the extent to which Featback contributed to these processes is inquired. Depending on whether the participant has sought help or not, the number of questions in this section ranges from three to five; they are either open or yes-no questions. Finally, participants are inquired as to the frequency of visiting websites other than Featback in relation to their (eating) problems, visiting and/or using a forum, or making use of online support service in relation to their (eating) problems.

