#### Satisfaction and intervention usage analyses

(H5) To examine the fifth hypothesis that Featback with weekly expert-patient support results in an increased satisfaction and intervention usage, an ANOVA will be conducted to compare mean scores of satisfaction and intervention usage at T1 (i.e., directly after the intervention) between the three active intervention conditions. We correct for multiple testing for these analyses using Holm’s method.

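### Satisfaction is described as satisfaction with Featback, yet the analysis for H5 averages it over three arms, one of which does not receive Featback

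*Protocol article*

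**What the plan says.** All references are to the protocol article.

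- **User satisfaction** (secondary outcome measures) gives the purpose of the self-made instrument: "To assess the user satisfaction of Featback, a questionnaire was developed". The overall items it describes ask "how they rate the quality of support they have received from Featback, whether Featback helped them to more effectively cope with their eating-related problems", and how satisfied participants were with Featback in general. The section adds that "participants are requested to rate the various components of Featback".
- **Help-seeking attitudes and behavior questionnaire** covers attitudes to professional help, intention, actual help-seeking and use of other online services. For intention and actual help-seeking, "the extent to which Featback contributed to these processes is inquired".
- **Design** gives the third condition as "3) weekly individualized support by an expert patient through e-mail or chat". Aims and research questions describes the same arm as support without Featback.
- **Aims and research questions, H5** predicts higher usage and satisfaction for Featback with weekly expert-patient support than for Featback alone.
- **Satisfaction and intervention usage analyses** tests H5 by an ANOVA that will "compare mean scores of satisfaction and intervention usage at T1 (i.e., directly after the intervention) between the three active intervention conditions", with Holm's method for multiple testing.

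**The concern.** A mean can be compared across arms only if the items have the same object in each arm. Here the described object is Featback, and one of the three compared arms is defined by not receiving it. Participants are not blinded and are told their condition, so those in the support-only arm would know that they had not been allocated to the programme named in the items. They might rate it low, rate the expert patient in its place, or skip the item. In none of these cases is their mean a like-for-like comparator.

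Two things are at stake. First, a significant three-arm F test could reflect the wording and not any difference in satisfaction, and it could be reported as support for H5. Second, expert patients are told to encourage participants with severe symptoms to seek professional help (Ethical considerations), but the attribution item as described has nowhere to record their contribution in the support-only arm.

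**Working it through.** The plan gives no figure to reproduce. The check sets the sections side by side and then illustrates the size.

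**Step 1: object of the items against what each active arm receives**

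| Condition | Receives Featback | Receives expert patient | Overall Featback items have an object | In the H5 hypothesis | In the H5 ANOVA |
|---|---|---|---|---|---|
| 1 Featback | yes | no | yes | yes | yes |
| 2 Featback + support | yes | yes | yes | yes | yes |
| 3 Support only | no | yes | no, as described | no | yes |

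The mismatch is confined to condition 3, which enters the test although the hypothesis does not call for it.

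**Step 2: how far a non-comparable third mean can drive the omnibus test**

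Inputs:
- 88 per condition and 25% dropout between T0 and T1 (Sample size calculation): 88 × 0.75 = 66 observed per arm.
- True satisfaction equal in conditions 1 and 2, so H5 is false.
- Wording shift of s SD in condition 3. This is an assumption; the document offers no value, so two are shown.
- Alpha 0.05, and 0.025 as the first Holm step. The latter assumes that the Holm family is the two outcomes, satisfaction and usage.

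For arm means (0, 0, s) in SD units, the noncentrality of the one-way F test is λ = n·Σ(μᵢ − μ̄)² = n·(2/3)·s², with 2 and 3 × 66 − 3 = 195 degrees of freedom. The critical values are 3.04 at 0.05 and 3.76 at 0.025.

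| s (assumed) | λ | P(significant) at 0.05 | P(significant) at 0.025 |
|---|---|---|---|
| 0.5 | 66 × 0.6667 × 0.25 = 11.0 | 0.85 | 0.77 |
| 0.3 | 66 × 0.6667 × 0.09 = 3.96 | 0.41 | 0.30 |

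Without any shift these probabilities would be 0.05 and 0.025. A direct contrast of condition 2 with condition 1 uses neither the third mean nor its shift. It keeps its nominal error rate if its error variance is taken from those two arms.

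**Step 3: help-seeking**

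The items on the usefulness of, need for and knowledge of professional help, on intention and behaviour, and on other websites, forums and support services do not ask the respondent to rate Featback. They mean the same in every arm. Only the attribution item names Featback. No hypothesis or analysis in the article uses that item, so the consequence is descriptive.

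**The case against.** The strongest reply is that the questionnaire itself is not shown. The article summarises it in a few lines, the examples are introduced with "Among other questions, participants are asked how they rate the quality of support they have received from Featback", the table of assessments is not available here, and arm-specific wording is the kind of detail an article leaves to the full protocol. The article also sometimes uses Featback almost as the project's name. This stands as a limit on certainty. A reader might infer that support-only participants actually rate a programme they never received; the document does not establish that. What it does state is a Featback-specific measure and a three-arm comparison on it, and those two statements do not fit together as written.

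A reader might also infer that the expert patient is not rated at all. The text does not support this. The items include quality of support, components are rated, and the Background (E-mental health) describes the programme in these terms: "It contains psychoeducation, a fully automated symptom monitoring and feedback system, and weekly chat or e-mail contact with a coach". Support may therefore already be rated as a component in the combination arm. Nor can both custom questionnaires be said to ask only about Featback, since most help-seeking items do not.

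Finally, H5 compares two arms that both receive Featback, so its own contrast is sound. This also stands. The difficulty lies in the test chosen for H5. The SD shifts are assumed, and the calculation shows what a mismatch could do, not that one exists.

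**Conclusion.** The point holds in a limited form. As described, the overall satisfaction items refer to Featback, and the ANOVA for H5 includes an arm without Featback. The support-only mean is therefore not comparable with the other two and can drive the omnibus result. One help-seeking attribution item shares the fault. The contrast that H5 states, condition 2 versus condition 1, is not invalidated, and the remaining help-seeking items are unaffected.

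The probabilities of 0.85 and 0.77 (0.5 SD) and 0.41 and 0.30 (0.3 SD) rest on an assumed wording shift, 66 observed per arm, equal satisfaction in the two Featback arms and, for the second figure of each pair, a Holm family of two. The conclusion also assumes that the items are given in condition 3 as the article describes them. Severity is minor: one arm of one secondary analysis and one descriptive item, with no bearing on the primary outcome.

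**What to change.** 1. Test H5 on satisfaction as a pre-specified contrast of condition 2 versus condition 1, with the error variance taken from those two arms.
2. Include the support-only arm in a satisfaction comparison only on overall items worded identically in all three active arms, for example referring to 'the intervention you were allocated to'. State in the protocol which wording that arm completes.
3. Ask the help-seeking attribution item separately for Featback and for the expert patient, each shown only to those who received that component.
4. Recruitment began on 8 October 2018, so check what support-only participants have answered so far. If they answered Featback-worded items, flag the questionnaire version and leave those scores out of the between-arm satisfaction comparison. If they already had suitable wording, keep the scores and describe the wording.

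The cost is small. Both questionnaires are self-made and online, so no validated scale changes; the work is item wording and display logic. The downside is a version indicator in the data and, if step 4 applies, fewer usable support-only satisfaction scores.

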##### Help-seeking attitudes and behavior questionnaire

A custom-made questionnaire was developed to assess help-seeking attitudes and behaviors. Participants are presented with three 7-point Likert scale questions (ranging from 0 ”not at all applicable” to 6 ”fully applicable”) concerning the extent to which they believe professional help is useful, they need professional help themselves, and they know where to find help. Furthermore, intention to seek professional help and actual help-seeking behavior are assessed, and the extent to which Featback contributed to these processes is inquired. Depending on whether the participant has sought help or not, the number of questions in this section ranges from three to five; they are either open or yes-no questions. Finally, participants are inquired as to the frequency of visiting websites other than Featback in relation to their (eating) problems, visiting and/or using a forum, or making use of online support service in relation to their (eating) problems.

##### Intervention usage

Intervention usage will be operationalized by the amount of weekly monitoring assessments a participant has completed during the intervention period (range 0–8). Additionally, to be able to further investigate the relation between intervention usage and the effectiveness of Featback, the number of received support sessions of participants (one for each received e-mail or chat session) will be recorded.

